### Study Procedures

After screening, eligible participants will be enrolled and they will complete baseline assessments. Thereafter, participants will be randomly assigned to either an EA experimental group or a sham control group. EA or sham treatments will be given twice weekly for 8 weeks—a total of 16 sessions. Participants in both groups will receive routine chemotherapy provided by their oncologists, which will include the use of cytotoxic drugs. Participants will be assessed at the following timepoints (see Figure 2): baseline (T0), midpoint of main treatment (T1-T3) once every 2 weeks, and end of the 8-week main treatment (T4). Assessments include MoCA [24] + Functional Assessment of Cancer Therapy-Cognitive function (FACT-Cog) [25] for cognitive performance, FACT/Functional Assessment of Chronic Illness Therapy-Fatigue (FACIT-Fatigue) [26] for fatigue, European Organization for Research and Treatment of Cancer QoL Questionnaire-Core 30 (EORTC QLQ-C30) [27] for QoL, and Functional Assessment of Anorexia-Cachexia Therapy (FAACT)/FACT-Biologic Response Modifier (FACT-BRM) [28] for chemotherapy-related side effects. Assessments will be done prior to any procedures in that visit, including disease assessment and physician consultation.

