#### Sample Size Estimation

A total of 168 older patients with cancer will be recruited, of which 84 will be in the experimental group (EA) and 84 will be in the control group. Sample size calculation:

n = [p1 (1 – p1) + p2 (1 – p2)]/(p1 – p2)] × Cp.power

Cp refers to the process capability index. In the 2-sided test, Cp.power = 10.5 when *P*<.05 is met. n is the number of patients to be recruited in each group, p1 and p2 represent the incidence in each group, and a mean difference with 95% level of significance (α) and 80% power (1 – β) is set. In older patients with cancer, the incidence of chemobrain after chemotherapy is 30%, and the reduction of chemobrain could be 10%-20% with acupuncture intervention. The sample size for each group is 84 participants, considering a 20% dropout. Therefore, the overall target sample size of 168 will be included.

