### Statistical Analyses

Cognitive impairment is defined as those with SD>1.5 in the mean scores of MoCA and the QLQ-C30 at baseline for all participants at different timepoints. A time-series test in the Kaplan-Meier survival analysis will be used to compare the incidence of cognitive deficits accumulated after 8 weeks of acupuncture intervention between the 2 groups. Linear mixed-effects modeling will be used to compare participants’ cognitive impairment, fatigue, and depression at baseline, during, and after acupuncture intervention, where only those who have completed at least one assessment at baseline and during treatment will be compared. This model will use time and group as categorical fixed factors and random intercepts and use random intercepts in conjunction with a measurement covariance matrix. Participants’ age, chemotherapeutic drug dosage, fatigue at baseline, depression, and additional treatments will be considered as covariates in the statistical analyses. A 2-sided *t* test will be used to compare the covariates at each timepoint between the 2 groups. The chi-square test will be used for qualitative information and the *t* test will be used for continuous information at baseline. Statistical significance will be considered at *P*<.05. The study data used will be statistically analyzed using SPSS software (IBM Corp) under the supervision of a statistician. To ensure the privacy of the patients, all relevant study data and personal data will be kept in a locked file cabinet. Electronic data will be stored on an encrypted computer and will not be stored on any external storage device. Each participant will be assigned his or her own ID in the study record, which will be used in lieu of his or her name and personal identifying information. Clinical data from the study will be kept in a separate file from the participant’s personal data. The principal investigator will be responsible for all the clinical trial data. During and after the clinical trial, the principal investigator, researchers, and the ethical review committee have the right to view the study data. Participants will have the right to access their personal data and the results of the study. All study data will be stored for a minimum of 3 years after the completion of the trial, after which they will be destroyed in accordance with the rules of the ethics review committee.

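### The mixed model excludes randomised patients with no on-treatment assessment; the model does not need this rule, which can bias the change comparison slightly if early loss differs by arm and depends on baseline score

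*Protocol article*

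**What the plan says.** The mixed model in the Statistical Analyses section compares "cognitive impairment, fatigue, and depression at baseline, during, and after acupuncture intervention", and the same sentence limits who enters it: "where only those who have completed at least one assessment at baseline and during treatment will be compared". The structure is then given: "This model will use time and group as categorical fixed factors and random intercepts". Baseline is thus one of the compared time points and part of the response. The listed covariates include baseline fatigue and depression, but not baseline MoCA.

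The order of events is in Study Procedures: "After screening, eligible participants will be enrolled and they will complete baseline assessments. Thereafter, participants will be randomly assigned". The Blinding section agrees, since the envelope is opened only after baseline has been completed. The visits are "baseline (T0), midpoint of main treatment (T1-T3) once every 2 weeks, and end of the 8-week main treatment (T4").

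Sample Size Estimation sets 84 per arm, "considering a 20% dropout". The article does not say how many patients are expected to have no on-treatment assessment. It names no other analysis population for the mixed model. The Assessments section says only that dropouts will be recorded.

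**The concern.** Randomisation makes the arms comparable as allocated. A rule that depends on what happens afterwards can undo that. A patient who follows the schedule always has a baseline assessment, so only the requirement for an on-treatment assessment can remove anyone.

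Suppose one arm loses more of its low-scoring patients before their first on-treatment visit. The retained patients in that arm then start higher than those in the other arm and, by regression to the mean, appear to gain less. That difference enters the treatment contrast although the treatment did nothing. A likelihood analysis that keeps the baseline values of these patients corrects for it when loss depends on baseline, and needs no extra data. The rule gives up this protection and gets nothing in return.

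**Working it through.** **Inputs from the article.** 84 per arm; 20% total dropout; baseline before allocation; baseline in the response; five time points. No figure is given for the share of patients with no on-treatment assessment, so there is no plan figure to reproduce on this point.

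**How many patients could be removed.** If all planned dropout fell before the first on-treatment visit, 0.20 × 84 = 16.8 per arm would be removed, leaving about 67 per arm (134 in total). That is the ceiling. If dropout were spread evenly over the four two-week intervals (an assumption), about 20%/4 = 5% would leave before the first visit, or 0.05 × 84 ≈ 4 per arm.

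**Size of the bias.** Work in SD units with correlation ρ between baseline and week 8. If exclusion raises the retained baseline mean in one arm by δ and there is no true effect, then

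- bias in the difference in change = −(1 − ρ)δ
- bias in the week-8 difference = +ρδ

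The simulation had no true effect, 84 per arm, early loss in one arm only with probability proportional to exp(−1.5 × baseline z), and 4,000 replicates. Everything except the 84 is an assumption.

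| Early loss, one arm | ρ | Bias, excluded | Bias, kept | Implied δ = \|bias\|/(1 − ρ) |
|---|---|---|---|---|
| 5% | 0.5 | −0.034 | −0.002 | 0.068 |
| 5% | 0.7 | −0.018 | 0.002 | 0.060 |
| 10% | 0.5 | −0.063 | −0.001 | 0.126 |
| 10% | 0.7 | −0.037 | 0.000 | 0.123 |
| 20% | 0.5 | −0.127 | 0.000 | 0.254 |
| 20% | 0.7 | −0.077 | −0.002 | 0.257 |

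The implied δ agrees across the two values of ρ, as the formula requires.

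**False-positive rate.** The SE of the change contrast is √(2(1 − ρ)) × √(1/84 + 1/n), where n is the number retained in the arm with loss.

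- 5% loss, ρ = 0.5: n = 79.8, SE = 0.156, shift 0.034/0.156 = 0.22 SE, two-sided error about 5.5%. At ρ = 0.7 it is about 5.3%.
- 10% loss, ρ = 0.5: n = 75.6, SE = 0.158, shift 0.063/0.158 = 0.40 SE, about 6.8%. At ρ = 0.7 it is about 6.1%.
- 20% loss, ρ = 0.5: n = 67.2, SE = 0.164, shift 0.127/0.164 = 0.78 SE, about 12%. At ρ = 0.7 it is about 9%.

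Simulated rates are close: about 5-6% at 5% loss, 6.5-8% at 10%, and 10-13% at 20%.

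**Second simulation, five visits.** Assumptions: SD 3 points, within-patient correlation 0.6, compound symmetry, 2,000 runs, loss depending on baseline in one arm. Excluding baseline-only patients biased the difference in change by −0.07, −0.14 and −0.24 points at about 5%, 10% and 20% loss. Divided by 3, these are about 0.02, 0.05 and 0.08 SD. The week-8 difference was biased by +0.12, +0.22 and +0.37 points. With these patients kept, every bias was 0.01 points or less.

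**When the rule does no harm.** With completely random loss of 20%, neither analysis is biased and precision hardly changes (SE of the change difference 0.467 excluding, 0.458 keeping). With 20% loss in each arm and the same dependence on baseline, the bias is about zero and the error rate about 5.6-6.1%.

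**When keeping the patients is not enough.** If loss in the five-visit set-up depends on the unobserved week-2 score (20% loss), keeping them leaves a bias of 0.12-0.13 points. Excluding them gives −0.02 in change but +0.34 at week 8.

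**The case against.** The strongest reply is that few patients are involved. The first on-treatment assessment comes two weeks after randomisation, and anyone seen once stays in. A reader might take the planned 20% dropout as the share excluded, and the 9-13% false-positive rate as the expected error. The article does not support that: its 20% covers the whole trial, and the high error rate also needs all the early loss in one arm with steep selection on baseline. With milder selection, exp(−0.5z), even 20% against 0% gives 0.04-0.06 SD and an error rate of 6.4-7.2%. This part of the objection stands.

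The premise of differential loss is also thin. A reader might infer a heavier needling burden in the experimental arm from the added abdominal points. The Abstract and the Acupuncture Group section describe those points for that arm only, whereas the Control Group section says the procedures differ only in the electrified pairs. These passages must be reconciled, and meanwhile the argument can rest only on 6 against 1 electrified pairs. Participants are to be blinded and both arms have 16 sessions, so nothing in the article shows that early loss will differ.

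Nor does the rule necessarily favour electroacupuncture. If that arm lost more low scorers, the change contrast on MoCA would be biased against it, although the week-8 difference would move the other way.

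A baseline-plus-one-visit set is a familiar modified intention-to-treat definition, and an analysis plan that is not shown may say more. But this article states the restriction outright, so it is not something merely left to another document. Had an outcome's own baseline entered only as a covariate, baseline-only patients would add almost nothing. The article instead compares the outcomes at baseline as well as later.

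**Conclusion.** The point holds as an inexpensive improvement, not as a serious flaw. The stated rule removes randomised patients on post-randomisation grounds, and the planned type of model does not need it. Bias requires two conditions together: early loss that differs between arms, in amount or in its dependence on baseline, and a link between that loss and baseline score. The article establishes neither. If both hold, the plausible bias in the change contrast is about 0.02-0.06 SD for 5-10% one-arm early loss, with a false-positive rate of about 5-8%. The 0.07-0.13 SD and 9-13% at 20% are a ceiling. All these figures rest on assumed correlations, selection and loss.

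It would also be too strong to say that keeping the patients removes the bias in general. It does so when loss depends on observed data. When loss depends on unobserved scores, bias can remain either way.

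**What to change.** Replace the restriction in Statistical Analyses with:

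*All randomised participants with at least one assessment, including baseline only, are analysed in the group to which they were randomised, by (restricted) maximum likelihood with baseline in the response and a group-by-time term.*

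Add that this analysis is valid when loss depends on observed data. Keep the restricted set as a sensitivity analysis, and there say whether a patient seen only at T4 counts as assessed during treatment, since the article calls T4 the end of treatment.

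The cost is one or two sentences, no new data and the same SPSS procedure. At the article's last count 11 of 168 participants had been recruited. The gain is small if early loss turns out to be rare or balanced.

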### Specific Aims and Hypotheses

Chinese acupuncture is an emerging therapeutic option for chemotherapy-induced cognitive impairment in older patients with cancer, despite limited supporting evidence [23]. This study has 2 specific aims.

First, to evaluate the clinical therapeutic response of EA intervention for the treatment of chemobrain in older patients with cancer, a randomized controlled trial is designed to study the effects of EA on chemobrain at baseline, 2, 4, 6, and 8 weeks follow-up. We hypothesize that those assigned to EA will show greater reductions from baseline to follow-ups in MoCA Overall Anxiety Severity and Impairment Scale and Digit Span Test scores and greater reductions in cognitive impairment in daily responsibilities relative to the control group. We also hypothesize that the effectiveness of EA on QoL and multiple functional assessments will be similar across experimental or control groups.Second, our aim is to elucidate the modern biomedical mechanism of EA in the treatment of chemobrain in older patients with cancer. In testing the putative mechanisms of action, we hypothesize that the intervention effects on study outcomes will be mediated by reductions in chemotherapy-induced working memory impairment and the incidence of certain digestive, neurological, and distress-related symptoms.

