### Assessments

In this study, therapeutic efficiency will be assessed in terms of the following aspects: cognitive performance, fatigue, QoL, and chemotherapy-induced side effects. The primary outcome of this study is to verify whether EA is therapeutically useful for preventing chemobrain and alleviating the related symptoms and the safety of intervention. Cognitive performance will be assessed using MoCA + FACT-Cog. The secondary outcomes are as follows: QoL will be measured using EORTC QLQ-C30, fatigue will be assessed using the FACIT-Fatigue scale, and the manifestation of chemotherapy-induced side effects will be assessed using the Chemotherapy Symptom Rating Scale FAACT + FACT-BRM. All assessment scales will be evaluated by previously trained researchers at the following timepoints (see Figure 2): baseline (T0), midpoint of main treatment (T1-T3) once every 2 weeks, and end of the 8-week main treatment (T4) (a total of 5 timepoints). We will also keep a record of all the shedding cases. This study is a multidisciplinary clinical trial (across oncology and Chinese medicine disciplines) on the role of Chinese acupuncture as therapy for chemotherapy-induced cognitive impairment in older patients with cancer. If successful, findings from this study might have beneﬁts in reducing chemotherapy-induced working memory impairment. Data from this study may be used to support an implementation and dissemination trial of Chinese EA in real-world behavioral health and social service settings.

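### The mixed model as written has no group-by-time term and includes the pre-randomisation visit as a response, so its group term understates the effect and does not match the change-from-baseline hypothesis

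*Protocol article*

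**What the plan says.** The Statistical Analyses section describes one longitudinal model for cognitive impairment, fatigue and depression, covering outcomes "at baseline, during, and after acupuncture intervention". On its terms it says: "This model will use time and group as categorical fixed factors and random intercepts". It adds a measurement covariance matrix and lists covariates: age, drug dosage, baseline fatigue, depression and additional treatments. Baseline MoCA is not listed.

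Entry to the model is restricted: "only those who have completed at least one assessment at baseline and during treatment will be compared". Every analysed patient therefore contributes a T0 value.

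The Assessments section gives "a total of 5 timepoints", T0 to T4. Study Procedures puts T0 before allocation: "eligible participants will be enrolled and they will complete baseline assessments. Thereafter, participants will be randomly assigned".

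Specific Aims and Hypotheses says that patients assigned to electroacupuncture "will show greater reductions from baseline to follow-ups" relative to control. The Introduction names change in MoCA score as a primary outcome, alongside adverse events.

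**The concern.** A greater change from baseline in one arm than in the other is a group-by-time contrast. A model whose fixed part is time plus group holds the arm difference equal at all five visits. One of those visits precedes randomisation, so its true difference is zero. The single group coefficient is then a weighted mean of five differences, one of which carries no treatment effect.

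The reported difference would be smaller than the effect on treatment, would take in part of any chance difference at T0, and would use the repeated measures inefficiently. No other analysis stated in the article compares score change between arms. The Kaplan-Meier comparison concerns incidence of deficits, and the t and chi-square tests are described for covariates and baseline data.

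**Working it through.** The plan gives no figure for this model, so there is none to reproduce. The check works out what the group coefficient estimates.

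**Inputs from the article.** Five visits, one of them pre-randomisation (Assessments; Study Procedures). 84 per arm and 20% dropout (Sample Size Estimation), so 84 × 0.8 = 67.2, taken as 67 per arm.

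**Assumptions not in the article.** Complete data at the five visits, equal variances, effect d = 0.4 SD, within-patient correlation ρ = 0.6 (range 0.5 to 0.8), and two shapes of effect over time.

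**Step 1: what the group term estimates.** With random intercepts and complete data, each visit has weight 1/5.

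- Constant effect from week 2: d × (0 + 1 + 1 + 1 + 1)/5 = 0.80d.
- Linear growth to d at week 8: d × (0 + 0.25 + 0.5 + 0.75 + 1)/5 = 0.50d.
- Chance difference b at T0 only: b/5 = 0.20b. This is the direct share of T0; later scores correlate with T0 and carry some of the imbalance too.

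**Step 2: sensitivity to the covariance matrix.** The article does not specify the matrix. With AR(1) residuals of 0.5 (assumed), the visit weights are proportional to 1, 0.5, 0.5, 0.5, 1, so T0 has weight 1/3.5 = 0.286. The term becomes 0.714d under a constant effect, stays at 0.50d under linear growth, and takes in 0.286b.

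**Step 3: power.** Two-sided 5%, power = Φ(effect/SE − 1.96), with n = 67, d = 0.4, ρ = 0.6 and compound symmetry.

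| Contrast | Variance | SE | Power, constant | Power, linear |
|---|---|---|---|---|
| Group term as written | (2/67)(1+4ρ)/5 | 0.1425 | 61% | 29% |
| Week-8 change from baseline | (2/67) × 2(1−ρ) | 0.1545 | 74% | 74% |
| Week 8, baseline-adjusted | (2/67)(1−ρ²) | 0.1382 | 82% | 82% |
| Average post-baseline change | (2/67) × 1.25(1−ρ) | 0.1222 | 91% | 53% |
| Average post-baseline, baseline-adjusted | (2/67)[(1+3ρ)/4 − ρ²] | 0.1007 | 98% | 70% |

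For the first row the effects are 0.8 × 0.4 = 0.32 and 0.5 × 0.4 = 0.20. For the average contrasts under linear growth the effect is (0.25 + 0.5 + 0.75 + 1)/4 × 0.4 = 0.25.

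**Step 4: range over the correlation.** As ρ goes from 0.5 to 0.8:

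- group term as written: 67% down to 52% (constant), 32% down to 24% (linear);
- week-8 change contrast: 64% up to 96%;
- baseline-adjusted week-8 contrast: 76% up to 97%.

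**The case against.** The strongest reply is that the omission is only silence. The sentence names factors; it does not say main effects only, does not exclude an interaction, and does not make the group coefficient the test. The article is condensed, and a full plan may contain the interaction. This stands in part: a reader might infer that an interaction has been ruled out, and the text does not support that. But the article does set out the fixed factors, random part, covariance and covariates, and a model fitted from that description lacks the term its own hypothesis needs.

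Other stronger readings also fail.

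- **Invalid test.** A reader might infer inflated type I error. Randomisation balances T0 in expectation, so the group term still tests a true null correctly.
- **Week 8 as the set target.** The hypothesis speaks of follow-ups in the plural and the article does not single out week 8 for MoCA. The factor 0.5 is relative to the week-8 effect only.
- **Random intercepts alone.** The section adds a measurement covariance matrix, so the covariance structure is not open to that criticism.
- **All the lost power is due to the missing interaction.** The gap from 61% to 82% also includes baseline adjustment; the unadjusted week-8 change contrast has 74%. At ρ = 0.5 with a constant effect, the group term (67%) even exceeds that contrast (64%), although the average change contrast has 83%.
- **An underpowered trial.** The trial is sized on incidence proportions and the article does not call the mixed model primary, so these figures do not describe the analysis behind the sample size.

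**Conclusion.** The point holds as a fault in the stated model. The fixed part has no term for differential change, and T0 is in the response without a common baseline mean or adjustment for baseline MoCA. If the group term is read as the treatment effect, it is 0.8 of a constant effect or 0.5 of a linearly growing week-8 effect, with 20% of any T0 imbalance added directly. Those factors need only complete data and random intercepts; AR(1) residuals of 0.5 change them to 0.71, 0.5 and 29%.

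The loss of power is likely but its size is uncertain. It depends on the assumed effect, correlation, covariance and shape over time, and on which contrast is used for comparison. The harm is an attenuated estimate and reduced power, not a false-positive risk.

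**What to change.** Amend the mixed-model description in one of two ways:

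1. keep T0 to T4 as responses, add the group-by-time interaction and constrain the two arms to a common baseline mean; or
2. model T1 to T4 only, with group, time, their interaction and the baseline value of the outcome as covariate.

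In either case name before analysis the contrast to be tested: the week-8 difference or the average post-baseline difference. The choice matters, since in the table above the average contrast does better under a constant effect and the week-8 contrast under linear growth. If the full plan already contains the interaction, the article's description should be brought into line with it.

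The cost is one or two sentences. The data are already scheduled, the planned software can fit either model, and the article reports 11 of 168 participants recruited as of October 21, 2023.

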Acupuncture has been used for thousands of years in China and other Asian countries to treat various diseases, including sleep disturbance [12]. It is a nonpharmacological therapy that involves inserting needles into acupuncture points and sometimes applying minielectrical current stimulation on acupuncture points via needles or applying acupressure on the surface of points in different parts of the body, including ear and scalp [12]. Electroacupuncture (EA) is an effective family member of combo acupoint stimulation [13]. Lyu et al [14] reported that EA could be effective in alleviating various side effects caused by anticancer drugs, such as pain, vomiting, fever, fatigue, dry mouth, anxiety, depression, and insomnia. In addition, EA could promote the rehabilitation of pathological microstructures in the brain and improve the cognitive ability of patients with cognitive impairment. Clinical trials [14,15] of acupuncture for preventing and managing mild cognitive impairment in older adults show that it can improve the clinical efficacy rate, Mini-Mental State Examination Scale score, Montreal Cognitive Assessment (MoCA) test score, and clock drawing task scores, suggesting that acupuncture can be an effective approach complementary to existing therapies. Evidences [14] from acupuncture in patients after an ischemic stroke support its role in the treatment of neurological deficits through modulation of neuroplasticity. Chemobrain affects cognitive function, in particular, think and memory functions through various mechanisms, including inflammation and oxidative stress, which may lead to neurogenesis and glycogenesis reduction. This pathological process shares some similarities with brain damage after an ischemic stroke [3,16]. Therefore, it is important to investigate if EA is effective in preventing and treating chemobrain in older patients with cancer and for improving the QoL of cancer survivors.

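### Dosage, depression and additional treatments are covariates not limited to baseline, so the efficacy estimate may be conditioned on variables that treatment can change

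*Protocol article*

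**What the plan says.** The Statistical Analyses section of the protocol article states that participants' "age, chemotherapeutic drug dosage, fatigue at baseline, depression, and additional treatments will be considered as covariates in the statistical analyses". Of the five items, only fatigue carries an explicit baseline qualifier.

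The sentence that follows reads "A 2-sided *t* test will be used to compare the covariates at each timepoint between the 2 groups". Baseline comparisons, by chi-square and t test, have a separate sentence after it.

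The same section uses a linear mixed-effects model "to compare participants’ cognitive impairment, fatigue, and depression at baseline, during, and after acupuncture intervention". On its structure it adds: "This model will use time and group as categorical fixed factors and random intercepts". Depression is thus both an outcome of this model and a listed covariate.

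Two other sections bear on whether treatment can change these variables. The Introduction cites earlier work: "EA could be effective in alleviating various side effects caused by anticancer drugs, such as pain, vomiting, fever, fatigue, dry mouth, anxiety, depression, and insomnia". Specific Aims and Hypotheses, under the second aim, expects the effects to be mediated by reductions in working memory impairment and in "the incidence of certain digestive, neurological, and distress-related symptoms". Study Procedures adds that both groups receive routine chemotherapy while in the study.

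**The concern.** An efficacy trial estimates the total effect of assignment. Covariates fixed before randomisation leave that target intact and usually sharpen the estimate. A covariate measured afterwards is different. If assignment changes it, holding it constant takes out whatever part of the effect passes through it. If it also shares an unmeasured cause with the outcome, adjustment brings in further bias that randomisation would otherwise have excluded.

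Depression is the clearest case, because the article treats it as something EA may relieve and as part of the route by which EA may work. Dosage and additional treatments are less clear. Chemotherapy runs alongside the 8-week intervention, so delivered dose and added treatments can vary after randomisation, but the article does not say that EA alters them.

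At stake is the mixed-model comparison of cognition, fatigue and depression. Its group effect could be understated or overstated, and a reader could not tell which from the report.

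**Working it through.** The plan states no figure on this point, so the main check is a reading of the text. A simulation then shows the possible size.

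**Reading the text**

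1. Age and baseline fatigue have no new value at each visit, apart from the passage of time. A per-visit comparison of the covariates has content only if dosage, depression or additional treatments are recorded repeatedly.
2. Because baseline comparisons have their own sentence, the per-visit sentence is hard to read as a loose description of the baseline table.
3. Depression is modelled during and after the intervention, so post-randomisation values are planned.
4. Nothing in the article limits dosage, depression or additional treatments to planned or baseline values.

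**Illustration of size**

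From the Sample Size Estimation section: 84 per group and 20% dropout, so 84 × 0.80 = 67.2, or about 67 per arm. Everything else is assumed:

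- G is 1 for EA and 0 for control. M is a post-randomisation covariate scored so that higher is worse, with within-arm SD 1. Y is the outcome, with residual SD 1.
- M = −a·G + noise, where a is the reduction that EA produces in the covariate.
- Y = d·G − b·M + noise, where b is the harm per unit of the covariate and d is the effect not passing through it.
- Total effect = d + a·b, set at 0.50.

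Regressing Y on G recovers 0.50. Adding M gives d = 0.50 − a·b. If an unmeasured common cause worsens both M and Y with strength u, the adjusted value becomes 0.50 − a·(b + u²).

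Simulated means are from 3000 replicates, by linear regression at a single visit:

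| Case | a | b | u | Adjusted, by formula | Simulated, unadjusted | Simulated, adjusted |
|---|---|---|---|---|---|---|
| EA does not affect the covariate | 0 | 0.4 | 0 | 0.50 − 0 = 0.50 | 0.499 | 0.499 |
| Mild | 0.2 | 0.3 | 0 | 0.50 − 0.06 = 0.44 | 0.505 | 0.442 |
| Middle | 0.3 | 0.4 | 0 | 0.50 − 0.12 = 0.38 | 0.497 | 0.377 |
| Strong | 0.5 | 0.5 | 0 | 0.50 − 0.25 = 0.25 | 0.496 | 0.249 |
| Middle, with common cause | 0.3 | 0.4 | 0.5 | 0.50 − 0.3 × 0.65 = 0.305 | 0.505 | 0.307 |
| Reverse: EA raises a harmful covariate | −0.3 | 0.4 | 0 | 0.50 + 0.12 = 0.62 | 0.500 | 0.619 |

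The bias does not depend on the number per arm, which affects only precision. The reverse case could arise if, for example, more chemotherapy were delivered in the EA arm and this harmed cognition. The article gives no evidence for or against that.

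**The case against.** Several objections have force.

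- **Timing is inferred.** The baseline qualifier could be meant to cover depression as well as fatigue, and dosage could mean the planned regimen. The only depression scale named in the text is used at screening, and the full schedule of measures is in a figure that is not shown. The per-visit sentence is also loosely worded, since it nominally covers age and baseline fatigue. These readings are possible, but they fit that sentence poorly and nothing in the article confirms them.
- **The wording is not binding.** Saying that covariates will be considered commits none of them to a model, and covariate timing is often settled in the SAP. That is true, but the article names these variables and their per-visit testing. It does more than leave the matter open.
- **The pathway argument covers depression only.** The mediation hypothesis does not mention dose or additional treatments, and chemotherapy is described as routine care given by the patients' oncologists. This stands, and it limits the claim for those two variables to a conditional one.
- **The contrast between arms may be modest.** The control group also has needling and one charged pair, so the difference in depression between arms could be small. The case of no effect on the covariate would then be close to the truth.

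Stronger readings are tempting, but the documents do not support them. A reader might infer that the per-visit t tests decide which covariates enter the model; the text says only that covariates are compared. A reader might infer that the bias always runs toward zero; the reverse case shows otherwise. A reader might also infer that the baseline score of the outcome has been ignored; the mixed model already carries baseline as one of its responses.

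**Conclusion.** The point holds in a limited form. As written, the plan allows the efficacy model to be adjusted for variables that assignment can affect. For depression the case is strong on the article's own account, and the expected result is an understated effect. For delivered dose and additional treatments, bias depends on whether EA changes them, and its direction is open.

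With a true effect of 0.50 SD, the assumed cases give adjusted estimates of about 0.44 to 0.25 when EA improves the covariate, about 0.62 in the reverse case, and no bias when EA does not affect it. The effect size and the values of a, b and u are assumptions, and the calculation uses one visit, not the planned repeated-measures model.

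A reader might turn this into a loss of power for the trial. The documents do not support that step. The sample size rests on the incidence of chemobrain, that incidence is to be compared by Kaplan-Meier analysis, and no covariate adjustment is described for it.

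The plan should be changed, but the finding does not undermine the design.

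**What to change.** In the Statistical Analyses section, or in the SAP if one exists:

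1. Limit covariates in the efficacy models to values fixed before randomisation: age, baseline fatigue, depression at screening or baseline, and planned regimen or chemotherapy status at entry (already started or not yet started).
2. Do not use depression as a covariate when depression is the outcome. The same care applies to baseline fatigue in the fatigue model, because baseline is already among the modelled responses.
3. Report on-study depression, delivered dose and additional treatments descriptively by arm, or use them in a separate mediation analysis under the second aim.
4. Drop the per-visit t tests of covariates.

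This is a change of wording with no effect on sample size or visits. Age, baseline fatigue, the screening depression score and chemotherapy status at entry should already be available from baseline or eligibility assessment. Planned regimen would need to be recorded at entry if it is not already. Enrolment has begun, so the change should be dated and made before any unblinded data are seen.
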